### Sample size

In calculating the sample size, a power of 90% and an α value of 5% were assumed, to detect a mean change in pain intensity, measured on the 100 mm visual analogue scale, of 32.3 mm between the initial and final values among the experimental group, and a mean reduction of 19.8 mm among the control group (standard deviation 31.9 mm), on the basis of the results of a pilot experiment carried out beforehand at the Pain Treatment Unit at the Dos Hermanas Healthcare Clinic between April and December 2006. These assumptions require a sample size of 140 patients per group, in a design with two equal groups. We propose to recruit 400 patients in order to allow for a 30% drop out rate.

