#### Statistical analysis

A comparison will be made of the baseline variables for each of the groups, to test the homogeneity obtained from the random allocation to groups, in terms of differences of the means and of proportions. The magnitude of the difference in the possible imbalance produced by the random allocation between the two groups will be quantified in terms of ratios of the means and of proportions (using that of the placebo group as a reference level), and the final adjustment will be made by secondary analyses with multiple linear regression models.

In the unadjusted analysis, significance tests will be performed for comparison among k samples (parametric or otherwise, depending on whether or not the distribution of the outcome variables is asymmetric, and on the homogeneity of their variances), taking that of the placebo group as a reference level, and using comparison tests for differences of the means in the primary outcome measure (pain intensity on the 100 mm VAS), both for the inter-group comparisons (for independent samples) and for comparisons between the initial and final levels in each group (in this case, using tests for non-independent or paired samples).

Linear regression models will be constructed for the primary outcome measure, adjusted by the baseline level and using ITT analysis. The group variables will be included, taking that of the placebo group as a reference level, together with the results recorded by the medical professionals, and the sociodemographic data (age and sex), and the baseline levels for the variables related to the severity of the process (pain intensity and frequency). Adjustments will be made for possible confounders, using criteria of statistical significance and of confusion. The detection of possible interactions with the treatment group variable will be evaluated using criteria of statistical significance for the corresponding interaction terms. The level of statistical significance will be set at α < 0.05. The model will be reconstructed, removing the observations with Cook's distances exceeding the 90^th ^percentile of the distribution, in order to test the consistency of the results.

An economic analysis will also be carried out, from the standpoint of the interests of the Andalusian Public Health System.

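### The Cook's-distance consistency refit deletes 10% of patients in every dataset, and its ordinary standard error is then about 25% too small; the all-patient ITT analysis is unaffected

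*Protocol article*

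**What the plan says.** The Statistical analysis section of the protocol article sets out the main model: "Linear regression models will be constructed for the primary outcome measure, adjusted by the baseline level and using ITT analysis". It fixes the test level, "The level of statistical significance will be set at α < 0.05", without saying whether the test is one- or two-sided. The next sentence adds that the model will be rebuilt after "removing the observations with Cook's distances exceeding the 90^th ^percentile of the distribution", and gives the purpose: "in order to test the consistency of the results".

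No reference distribution is named, so the natural reading is the empirical distribution of the trial's own Cook's distances. The section mentions no adjustment to the refit's standard errors and no criterion for calling the two fits consistent. The Discussion section confirms that the main result rests on ITT, with a per-protocol analysis alongside.

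**The concern.** Two features of the rule are wrong as written.

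- **It is relative.** A 90th-percentile cut-off always has 10% of observations above it. It removes a tenth of the patients from perfectly clean data just as it does from badly contaminated data, so the size of the deletion says nothing about whether influential observations exist.
- **It selects on the outcome.** Cook's distance is a squared residual multiplied by a leverage term. In a balanced two-arm trial leverage varies little, so the patients removed are mostly those with the largest residuals. This shrinks the residual variance that the refit reports, while the estimate itself can become more variable.

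At stake is the value of the check. If the refit's p-value or confidence interval is read at face value, it will look more precise than the full analysis for a purely mechanical reason. It will then tend to support significance, or appear to find it, where the data do not.

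**Working it through.** **Inputs from the Sample size section.** "a power of 90% and an α value of 5% were assumed"; mean reductions of 32.3 mm and 19.8 mm, a difference of 12.5 mm; SD 31.9 mm; 140 evaluable per group; 400 recruited for 30% dropout.

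**The plan's own figure first.**
- n per group = 2 × (1.960 + 1.282)² × 31.9² / 12.5² ≈ 136.9, so 137 (138 with the t distribution). The plan says 140, which gives power 0.906.
- 280 / (1 − 0.30) = 400.

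The sample size reproduces and is not in dispute.

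**Number deleted.** 0.10 × 280 = 28; 0.10 × 400 = 40. In every simulated trial with clean normal data exactly these numbers were removed. In 5,000 such trials with 280 patients the largest Cook's distance seen was 0.22, far below the common benchmark of 1.

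**Influence formula.** D_i = r_i² h_i / [p s² (1 − h_i)²], where r_i is the residual, h_i the leverage, p the number of coefficients and s² the residual variance. Deleting the largest D_i therefore deletes large |r_i|.

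**Simulation.** 10,000 trials per scenario, 1:1 allocation, residual SD 31.9 mm, 0 to 10 covariates. Each trial was fitted by OLS, observations above the empirical 90th percentile of D were dropped, and the model was refitted with ordinary standard errors and tested two-sided at 0.05.

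Normal errors, N = 280, one covariate, no treatment effect:

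| | Full model | Refit |
|---|---|---|
| Mean stated SE (mm) | 3.81 | 3.26 |
| Actual SD of the estimate (mm) | 3.83 | 4.37 |
| Rejection rate | 5.4% | 14.5% |

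- Ratio of stated to actual: 3.26 / 4.37 = 0.746, so the stated SE is about 25% too small.
- Cross-check: 2 × [1 − Φ(1.96 × 0.746)] = 2 × [1 − Φ(1.462)] ≈ 0.144, which agrees with the simulated 14.5%.
- With an assumed residual SD of 28.0 mm the picture is the same. Residual SD falls to 22.6 mm on refit, and the stated SE is 2.86 mm against an actual 3.84 mm (ratio 0.745).

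Rejection rates with no treatment effect, by assumed error shape:

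| Errors | Full model | Refit |
|---|---|---|
| Normal (N = 280 or 400) | 4.7% to 5.6% | 13.8% to 15.4% |
| Heavy-tailed (t, 5 df) or skewed (N = 280) | 4.6% to 5.4% | 11.8% to 12.6% |
| Uniform (N = 280) | 5.0% to 5.1% | 19.8% to 20.2% |

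**Direction of disagreement.** In the first table's setting, 10.0% of null trials turn from non-significant to significant on refit and 0.9% turn the other way: 5.37 − 0.88 + 9.99 = 14.48%.

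**Confirmation of false positives.** In that setting, (5.37 − 0.88) / 5.37 = 84% of false-positive full-model results remain significant on refit. Two smaller normal-error simulations of 4,000 and 5,000 trials gave 91% (4.2 / 4.6) and 92%. A fair statement is 84% to 92%.

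**Planned effect.** With a true difference of 12.5 mm and normal errors, the mean estimate is 12.5 mm before and after deletion.

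**The case against.** The strongest reply is about scope. The refit is a secondary check. The model on which the trial rests keeps all patients, is analysed by ITT and holds its 5% level. If the refit is used only to require that a significant main result also survives deletion, it cannot raise the trial's error rate. In a null simulation the full model rejected in 4.6% of trials, and both models together in 4.2%. The text also does not say that consistency is judged by the refit's p-value. Comparing coefficients is open, and with normal errors that comparison is unbiased. All of this stands, and it limits the point to the refit.

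Three stronger readings are tempting, and the protocol does not support them.

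- **The trial's false-positive rate is tripled.** That would need the refit to replace or override the full-data result. Nothing in the text provides for this.
- **Deletion biases the treatment effect.** Under an assumed responder/non-responder mixture the estimate did shift, from 12.6 to 16.1 mm in one set-up and from 13.6 to 17.5 mm in another. The protocol gives only means and one SD, with no outcome distribution, so these figures illustrate what could happen and do not predict it.
- **Leaving ITT is itself the error.** A sensitivity analysis need not be ITT, and a per-protocol analysis is planned anyway.

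The confirmation rate also needs care. Any check on the same patients agrees with most false positives, so a high rate alone proves little. What marks this check as faulty is the understated standard error and the lopsided switching towards significance.

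The objection does not rescue the rule itself. The percentile cut-off is stated explicitly, so this is not detail that an article would leave to a fuller document.

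**Conclusion.** The consistency refit is wrong as written and should be fixed; it does not threaten the main analysis. It removes 10% of patients in every dataset. With normal errors and 280 patients its ordinary standard error is about 25% too small, and a nominal 5% test rejects in about 15% of null trials (about 12% to 20% across the assumed error shapes). Because it switches towards significance far more often than away from it, agreement between the two fits reassures less than it seems to.

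This rests on three assumptions: a two-sided test, ordinary OLS standard errors in the refit (no others are described), and the empirical reading of the percentile. If a theoretical F distribution had been meant, almost no observation would be removed and the problem would largely vanish, but the text names none. The error shapes are assumed. The 25% figure does not depend on the residual SD chosen.

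**What to change.** Replace the percentile-deletion refit with a robustness analysis that keeps every patient in the main model. M-regression limits the weight of outlying outcomes; HC3 standard errors protect against unequal variances. Name the choice in advance.

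Use Cook's distance only to list the most outlying observations for data checking. A cut-off of 1 would flag almost nobody here, since the largest values seen with normal errors were about 0.2. Listing the highest few is more useful than any automatic exclusion.

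If a deletion refit is still shown, report how far the estimate moves, with no p-value or confidence interval, and state that the all-patient ITT model is the sole basis for inference.

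The cost is one or two sentences in the Statistical analysis section. No new data are needed, and the sample size and main analysis do not change.

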## Discussion

This is an experimental study in which treatment with auricular implants is compared with that given to a placebo group, set up in such a way that the patient has the sensation of being given the real treatment. This control group, due to the fact of receiving specific attention and due to the effects of sensorial stimulation (the pressure on the implants) may have some positive results. This circumstance is contrary to the study's initial hypothesis, but to some extent reflects the inevitable placebo effect.

In order to obtain a sufficient number of patients, the study is being carried out at various healthcare clinics. It will be necessary to perform a stratification function so that all the clinics will receive equal proportions of patients in each of the two treatment branches. The patients will be asked not to obtain any kind of alternative treatment, but they will be allowed to continue taking any analgesic or anti-inflammatory medication needed, depending on the pain intensity experienced.

An important limitation that may affect this study is that of non-compliance with the prescribed treatment; patients might not attend a treatment session for any of several possible reasons. The principle outcome measure will be based on ITT, but a per protocol analysis will also be performed.

The sample size has been calculated on the assumption of a 30% drop out rate, but it will be necessary to ascertain that no differential losses occur between the two treatment branches.
